#### Mental health providers

Following randomization, mental health providers working at or affiliated with enrolled LGBTQ community centers will be invited to register for the training. Eligible providers must (1) be 18 years or older; (2) provide or be planning to provide mental/behavioral health services (e.g., therapy, support groups, case management) to LGBTQ clients; and (3) be affiliated with an enrolled LGBTQ community center. In order to meet the third criterion, providers may either be employed or volunteer at a participating LGBTQ community center or be in the referral network of a participating LGBTQ community center (i.e., receive referrals or intending to receive referrals of mental health clients from the center). Mental health providers will be recruited by center leadership. Upon randomization, center leaders will distribute flyers to their employees, volunteers, and referral network providers to inform them of the study/training opportunity. Center directors will be asked to share information about the benefits of the study/training (e.g., continuing education credits, free training materials, financial incentive for assessments).

To be eligible to attend the training, mental health providers must provide consent and complete the baseline survey. Upon training launch, enrolled providers will be given instructions on how to access their respective training materials and, if applicable, live webinar training sessions. Regardless of their engagement with their respective training intervention or whether they remain affiliated with an LGBTQ community center, all providers will be contacted to complete follow-up surveys at 4-, 8-, 12-, and 24-months post-baseline. No concomitant interventions are prohibited for mental health providers enrolled in the trial.

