### Randomization

Upon receiving 90 signed memoranda of understanding, the 90 LGBTQ community centers will be randomized in a 1:1:1 ratio to receive one of the three implementation strategies. Randomization will be stratified by director report of anticipated staff participation. Specifically, high-attendance centers will be operationalized as those with greater than the median number of anticipated providers across the 90 enrolled centers whereas low-attendance centers will be operationalized as those that anticipate fewer than the median number of providers per center. Centers whose anticipated number of providers is at the median will be randomly and evenly divided across the two groups. The 15 effectiveness centers will be randomized separately to ensure their equal distribution across the three implementation strategies. Randomization allocation will be generated by the study statistician and assigned by the study coordinator. All participants and study staff will be unmasked to condition assignment, as necessitated by the study design.

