#### Local supervisors

Upon randomization, centers randomized into the Local Supervision condition (described below) will be asked to nominate an individual to serve as the local supervisor, who will champion the supervision, training, and sustainment of LGBTQ-affirmative CBT at their center. The local supervisors should have significant therapeutic experience and be comfortable and interested in (1) learning how to oversee other providers at their center as they learn to deliver LGBTQ-affirmative CBT and (2) training future mental health providers to deliver LGBTQ-affirmative CBT. Local supervisors will be asked to attend an additional 12-week LGBTQ-affirmative CBT leadership workshop following the conclusion of the live webinar trainings, in addition to answering survey questions at all five assessment time points. To be eligible to attend the leadership workshop, local supervisors must provide consent and complete the baseline survey. Local supervisors may be simultaneously enrolled as directors and/or providers.

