#### Provider implementation fidelity outcome analyses

We will summarize provider characteristics (e.g., volunteer status, length of SGM service) overall and by implementation strategy and assess for baseline imbalances. We will then compare the implementation outcomes for the Materials Only condition vs. Direct Training vs. Local Supervision. The primary implementation outcome is provider implementation fidelity (assessed via simulated practice responses) at 8-month follow-up; secondary outcomes include 8-month provider self-efficacy, competency, familiarity, and use of LGBTQ-affirmative CBT. For primary and secondary outcomes, will use mixed effects models [93] with the identity link function to compare the effect of implementation strategies. The fixed effects include the time effect and the time × implementation strategies interaction terms; the random effects include center and within-provider repeated measures. We will use the robust score test to assess whether the interaction terms are significantly different across the three strategies, with a 0.05 overall Type I error rate, and a 0.025 error rate for each of the two primary strategy comparisons. For secondary outcomes, we will compare implementation strategies with a 0.05 Type I error rate. We will re-run these analyses with 12- and 24-month outcomes to determine implementation maintenance.

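### Providers are recruited by center leaders after randomization, and local supervisors in one arm only may count among them, so the arms may differ in who enrolls; the stated primary model and safeguards do not clearly correct for this

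*Protocol article*

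**What the plan says.** Under Randomization, once all memoranda are signed, "the 90 LGBTQ community centers will be randomized in a 1:1:1 ratio to receive one of the three implementation strategies". The same section states that "All participants and study staff will be unmasked to condition assignment, as necessitated by the study design". Stratification uses one factor, the director's anticipated number of participating providers.

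Under Mental health providers, "Following randomization, mental health providers working at or affiliated with enrolled LGBTQ community centers will be invited to register for the training". The recruiter is named: "Mental health providers will be recruited by center leadership". The method is also named: "Upon randomization, center leaders will distribute flyers to their employees, volunteers, and referral network providers". The pool is open, since a provider qualifies by being employed or volunteering at the center, or may simply "be in the referral network of a participating LGBTQ community center". Consent and the baseline survey come after this step, because they are conditions for attending the training.

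Under Local supervisors, only centers already allocated to Local Supervision nominate a supervisor, who should have substantial therapeutic experience. "Local supervisors may be simultaneously enrolled as directors and/or providers".

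Under Provider implementation fidelity outcome analyses, provider characteristics are summarized by strategy and checked for imbalance, with no stated consequence. For the primary model, "The fixed effects include the time effect and the time × implementation strategies interaction terms"; center and within-provider repeated measures are random. Covariate adjustment is described only for clients, as a sensitivity analysis, under Effectiveness outcome analysis.

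**The concern.** In a cluster trial, randomization makes the centers comparable. It makes the people within them comparable only if they are identified before allocation is known, or by someone who does not know it. Neither condition is stated here. The person who spreads the invitation leads a center whose arm is already set, and in the Local Supervision arm the request for a supervisor reveals that arm at the recruitment stage. The arms also ask for different things: self-paced content, twelve weekly live hours, or these plus supervision. Leaders may therefore approach different people in different arms. Any resulting difference in provider experience or motivation would be confounded with strategy and could mimic or mask the hypothesized gradient.

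Two features add to this. Experienced supervisors are picked out in one arm only and may contribute to its primary outcome. And a model without a strategy main effect, taken literally, sets the same baseline mean in every arm. That constraint is justified when participants are enrolled before allocation, but not when they join after it.

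**Working it through.** **1. Order of events.** Memoranda signed → centers randomized → leaders send flyers, and Local Supervision centers name a supervisor → providers consent and complete baseline → training launch. The baseline measurement itself is therefore post-allocation.

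**2. The plan's own figures.** From Sample size justification: 0.14/√0.0439 = 0.668, which matches 0.67. The detectable difference is d = (z₀.₉₈₇₅ + z₀.₈₀)·√(2·DE/180), with DE = 1 + 5·ICC, taking 30 centers × 6 providers = 180 per arm and two-sided 0.025 (sidedness is not stated).
- ICC 0.01: 3.083·√(2·1.05/180) = 0.333, or 0.340 using t with 58 df. This matches the stated 0.34.
- ICC 0.1: 3.083·√(2·1.5/180) = 0.398, or 0.407 using t. The stated 0.46 appears only with an unstated provider loss of about 30–35%.

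The stated upper end is thus conservative. The present point does not depend on it.

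**3. Effect of the literal model under a baseline shift.** Assumptions not in the document: a stable difference D of 0.1–0.3 SD between two arms at both baseline and 8 months, within-provider correlation ρ of 0.3–0.7, no true strategy effect, and a random center intercept. The ICC is 0.01 or 0.1.

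For center means, variance v = ICC + (1−ICC)/6 and baseline-to-8-month covariance c = ICC + (ρ−ICC)/6. With a common baseline mean, the strategy estimate is the 8-month difference minus β times the baseline difference, where β = c/v. Its bias is (1−β)·D, and its SE is √(2v(1−β²)/30).

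Example, ρ = 0.5, ICC = 0.1, D = 0.2: v = 0.1 + 0.9/6 = 0.25; c = 0.1 + 0.4/6 = 0.167; β = 0.667; bias = 0.333 × 0.2 = 0.067 SD; SE = √(2·0.25·0.556/30) = 0.096; Type I error 6.2%.

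| ρ | ICC | β | Bias at D = 0.2 (SD) | Type I, D = 0.1 | D = 0.2 | D = 0.3 |
|---|---|---|---|---|---|---|
| 0.3 | 0.01 | 0.333 | 0.133 | 5.8% | 17.6% | 39.1% |
| 0.3 | 0.1 | 0.533 | 0.093 | 3.9% | 8.4% | 16.9% |
| 0.5 | 0.01 | 0.524 | 0.095 | 4.5% | 11.4% | 24.6% |
| 0.5 | 0.1 | 0.667 | 0.067 | 3.4% | 6.2% | 11.5% |
| 0.7 | 0.01 | 0.714 | 0.057 | 3.6% | 7.0% | 13.4% |
| 0.7 | 0.1 | 0.800 | 0.040 | 3.0% | 4.5% | 7.2% |

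The nominal rate is 2.5%. With a strategy main effect, the bias is 0 and the error 2.5% in every row. The SE becomes √(4(v−c)/30): 0.105 instead of 0.096 in the example, 0.125 instead of 0.102 in the first row, 0.082 instead of 0.077 in the last.

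**4. Selection on potential to improve.** Assume enthusiasm correlates 0.3 with 8-month change, and that one arm loses its least enthusiastic 20% or 40%. The mean enthusiasm of those remaining is 0.35 or 0.64 SD, so change differs by 0.3 × 0.35 = 0.105 or 0.3 × 0.64 = 0.19 SD with no strategy effect. A main effect leaves this untouched.

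**5. Supervisors.** Thirty supervisors against about 180 providers in that arm is at most 30/180 = 17%. Webinars (12 weeks), the gap (4 weeks) and the workshop (12 weeks) sum to about 28 weeks from training launch.

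**The case against.** Several stronger readings are tempting, and the document does not support them.

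- A reader might infer that leaders take consent or collect baseline data. They do not: consent is electronic and provider surveys are completed online. Leaders only recruit.
- A reader might infer that providers choose to enroll knowing their arm. The text does not say so. The benefits leaders are asked to mention are not arm-specific, access instructions come at training launch, and the unmasking statement gives no time. A common flyer may already be in use.
- A reader might infer that the model certainly constrains baselines. The sentence says what the fixed effects include. If time × strategy is coded over all five time points, baselines are already arm-specific, which would fit a power calculation based on change. Exact coding is often left to an analysis plan.

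For Direct Training versus Local Supervision, ordinary providers attend the same webinars and the workshop falls on supervisors, so deterrence by workload is least plausible there. Directors may double as providers in every arm, so senior dual-role staff are not unique to one. Enrolled providers are also followed regardless of engagement.

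These points limit the size of the problem and the certainty about the model. They do not change the stated sequence, the open pool or the one-arm nomination. The safeguards named act on the number of providers, on description, or after enrollment; none acts on who enrolls.

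**Conclusion.** The concern holds as a risk built into the stated order of recruitment, not as a demonstrated bias. Who enters the primary analysis is not protected by randomization, and no stated step corrects an imbalance if one arises. Its size and direction cannot be derived from the document.

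The figures above show sensitivity only. Under the literal model, an assumed stable shift of 0.2 SD raises Type I error per comparison to 4.5–17.6%, and 0.3 SD to 7.2–39.1%. These figures vanish if baselines are in fact arm-specific, so the wording must say which is meant.

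It would also go too far to infer that a strategy main effect cures the problem. It removes a stable baseline shift and nothing else; selection of providers who would improve more remains.

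**What to change.** **Where recruitment is still open:** have providers register, consent and complete baseline, using arm-neutral material, before their center's allocation is disclosed. Some providers may withdraw once they learn the format, and this could differ by arm, so count and report it.

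**In any case:**
1. State that the primary model has arm-specific baselines: add a strategy main effect, or say that the interaction already covers the baseline time point. The cost is a somewhat larger SE (0.105 against 0.096 in the worked example). This is consistent with the power calculation, which rests on change.
2. Adjust the primary analysis for pre-specified provider baseline characteristics that are already collected, such as volunteer status and time spent serving SGM clients.
3. Add a sensitivity analysis of the primary outcome excluding local supervisors. Say openly that, without nominees named before allocation in the other two arms, the exclusion is one-sided. Naming a would-be supervisor at all 90 centers before disclosure would make it symmetric, but is extra work for low-resource centers.
4. Report post-allocation recruitment, and possible selection on potential to improve, as a limitation.

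Items 1, 2 and 4 are changes of wording and analysis only; item 3 needs one additional model run.

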#### Local supervisors

Upon randomization, centers randomized into the Local Supervision condition (described below) will be asked to nominate an individual to serve as the local supervisor, who will champion the supervision, training, and sustainment of LGBTQ-affirmative CBT at their center. The local supervisors should have significant therapeutic experience and be comfortable and interested in (1) learning how to oversee other providers at their center as they learn to deliver LGBTQ-affirmative CBT and (2) training future mental health providers to deliver LGBTQ-affirmative CBT. Local supervisors will be asked to attend an additional 12-week LGBTQ-affirmative CBT leadership workshop following the conclusion of the live webinar trainings, in addition to answering survey questions at all five assessment time points. To be eligible to attend the leadership workshop, local supervisors must provide consent and complete the baseline survey. Local supervisors may be simultaneously enrolled as directors and/or providers.

#### Clients

Clients will be eligible to take part in Aim 3 of the trial if they (1) are old enough to consent to behavioral health services in their respective state, (2) self-identify as a sexual and/or gender minority (e.g., LGBTQ), and (3) are currently or have recently received (within the past four months) mental/behavioral health services from one of the 15 effectiveness sites. Clients enrolled at the first time point will be asked to complete surveys at baseline and 4-, 8-, 12-, and 24-months post-baseline to assess short-term and long-term change in mental health outcomes. New clients will also be enrolled at all subsequent assessment time points.

### Implementation strategies

Based on a review of implementation strategies [77], our formative research with stakeholders, and the current state of EBPs for SGM mental health [77], we deemed training providers in LGBTQ-affirmative CBT to be the most feasible and significant way to sustain its implementation. We will test three training implementation strategies: (1) Materials Only, (2) Direct Training, and (3) Local Supervision. These conditions will be additive, so that each level also receives the supports of the lower levels.

#### Materials only

A digital suite of training resources has been shown to promote EBP implementation in resource-constrained settings [78]. We have developed an online training platform that contains 12 modules of highly engaging content, including (1) professionally filmed and edited instructional lectures featuring our team of expert trainers based on the published treatment manual [39], (2) instructional animations created by a professional animator detailing central concepts of the treatment, (3) video demonstrations of treatment delivery featuring our expert trainers and LGBTQ actors, (4) downloadable client worksheets, (5) optional readings to enhance learning, and (6) interactive exercises. This online suite contains approximately 10–12 h of content hosted on the Coursera learning platform and is designed to be completed at the user’s own pace. Regardless of study condition, all providers will receive access to the platform and a physical or digital copy of the treatment manual [39]; providers randomized to the Materials Only condition will only receive access to the platform and manual. Providers in all conditions will retain access to the online platform throughout the entire follow-up period. Participants will receive email reminders about the training. Engagement and adherence will be monitored.

#### Direct training

Direct training will consist of 12 weekly 60-minute live webinars on delivering LGBTQ-affirmative CBT led by a team of four expert trainers. Training will include didactics, “how-to” videos for each module, role-plays, opportunities for questions and answers, and experiential learning activities, as informed by social learning theory [79–83]. In designing this training, we considered sequence, spacing, modality, and duration of activities, as informed by adult learning theories [84]. A waitlist-controlled trial of this training showed efficacy across provider outcomes when compared to waitlist [57]. Providers will be able to attend one of two training session times each week. Providers in both the Direct Training and Local Supervision conditions will receive access to the live webinars, in addition to access to the online training platform and therapist manual. Participants will receive email reminders about the training. Engagement and adherence will be monitored weekly.

#### Local supervision

Four weeks after the final direct training session, the 30 centers randomized to the Local Supervision condition will send their nominated local supervisors to the first of 12 remote leadership workshop sessions focused on LGBTQ-affirmative supervision, training, and sustainment. In the train-the-trainer format to be employed in the Local Supervision condition, expert clinicians will provide additional training to local supervisors with the goal of increasing their ability to train other local mental health providers into the future. This training strategy has the benefit of harnessing local expertise, potentially making LGBTQ-affirmative CBT more responsive to local realities [85–87]. The goal of the LGBTQ-affirmative CBT leadership workshop is to provide local supervisors at LGBTQ centers with the tools, skills, and knowledge to become leaders and experts in LGBTQ-affirmative CBT and to train and supervise mental health providers at their center in LGBTQ-affirmative CBT for sustainment of this practice locally. Participants will receive email reminders about the training. Engagement and adherence will be monitored weekly.

## Outcomes

Guided by the RE-AIM framework, we will assess both implementation and effectiveness outcomes across relevant center, provider, and client levels quantitatively and qualitatively. Quantitative assessments will be captured through surveys at baseline and 4-, 8-, 12-, and 24-months post-baseline. Semi-structured interviews with select providers, directors, and local supervisors will be conducted throughout the follow-up period to provide additional context for understanding quantitative findings.

### Implementation outcomes

In Aim 1, we will assess the implementation success of three LGBTQ-affirmative CBT implementation strategies across the 90 LGBTQ community centers. The primary implementation outcome is provider fidelity to LGBTQ-affirmative CBT using our validated “simulated practice” assessment [64]. Providers will watch two brief (3-minute) video clips of an SGM actor roleplaying a presenting concern and then briefly describe in writing the clinical approaches they would use to address the concern. Research assistants will then code responses to assess participants’ application of LGBTQ-affirmative CBT skills using our reliable (ICC = 0.87) and valid rating scheme (57). Secondary implementation outcomes include mixed-methods assessments of the reach, adoption, familiarity, modification, and maintenance of LGBTQ-affirmative CBT skills across centers (See Table 1 for operationalizations).

**Table 1 Tab1:** Measures

Outcomes	Measures	Data Source	Time point
Primary outcomes			
Implementation fidelity	∙ Simulated practice assessment [57] based on previous EBP research [117–120].	Provider simulated practice assessment	baseline, 4 m, 8 m, 12 m, 24 m
Secondary outcomes			
Reach	∙ Percentage of active clients who receive the EBP will be self-reported in provider surveys. Semi-structured qualitative interviews with providers will highlight reasons for stronger or weaker reach.	Provider surveys and qualitative interviews	4 m, 8 m, 12 m, 24 m
Adoption	∙ Percentage of providers who self-report practicing LGBTQ-affirmative CBT out of total who were trained. Semi-structured qualitative interviews with providers will highlight why and in what cases providers chose not to implement.	Provider surveys and qualitative interviews	baseline, 4 m, 8 m, 12 m, 24 m
Implementation	∙ Confidence with and use of LGBTQ-affirmative CBT skills will be measured using a scale adapted from the Counselor Activity Self-Efficacy scale [121] and Use of LGBTQ-affirmative CBT skills scales [57]. ∙ Modification of LGBTQ-affirmative CBT will be assessed by the Modification and Adaptation Checklist [122] and semi-structured qualitative interviews with providers.	Provider surveys and qualitative interviews	baseline, 4 m, 8 m, 12 m, 24 m
Maintenance	∙ Funding stability, environmental support, organizational capacity, and strategic planning will be measured by the Program Sustainability Assessment Tool [123] and semi-structured qualitative interviews with providers and directors.	Director surveys, provider surveys and qualitative interviews	4 m, 8 m, 12 m 24 m
Implementation determinants			
Inner setting	∙ Motivation for change, resources, and staff attributes will be measured by subscales of the Organizational Readiness for Change– Treatment Staff Version and Organizational Readiness for Change– Treatment Director Version [124].	Director surveys, provider surveys	baseline, 4 m, 24 m
Outer setting	∙ SGM Policy Climate (e.g., anti-LGBTQ laws/policies) will come from existing policy and attitudinal indices [35, 55, 125] linked to the municipality of each center. ∙ Community socioeconomic disadvantage and rurality (e.g., poverty, housing characteristics, unemployment, education) will come from the American Community Survey [126] and be linked to the county of each center. ∙ Mental health workforce characteristics (e.g., provider prevalence in each state, continuing education requirements of centers’ states) will derive from existing metrics [127]. ∙ Semi-structured qualitative interviews with providers and directors will inform assessment of the outer setting.	Secondary data, provider and director qualitative interviews	baseline
Intervention characteristics	∙ Directors’ and providers’ openness to adopting EBPs and perceived divergence between EBPs and current practice will come from the EBP Attitude Scale [128].	Director and provider surveys	baseline, 4 m, 24 m
Individual characteristics	∙ Provider, director, and client demographics (e.g., race/ethnicity, sexual orientation, gender) will be assessed via self-report questionnaires.	Provider, director, and client surveys	baseline, 4 m, 8 m, 12 m 24 m
Implementation process	∙ Implementation barriers and facilitators will come from interviews about staff planning, engagement, and execution, and other feedback on the implementation process [129]. ∙ Perceived appropriateness of the intervention and implementation strategy will be assessed with the Training and Adoption Barriers Scale [130] and the Intervention Appropriateness Measure [131]. ∙ Training engagement and satisfaction will be assessed via questionnaires designed for this study and an adapted version of the Client Satisfaction Questionnaire [132].	Director, provider, and supervisor qualitative interviews	4 m, 8 m, 12 m, 24 m
Implementation mechanisms			
Organization-level implementation targets	∙ Organizational norms of importance, expectations, and rewards of implementing LGBTQ-affirmative CBT will be measured with the Focus, Recognition, and Rewards subscales of the Implementation Climate Scale [133]. ∙ Organizational policies and communications about LGBTQ-affirmative CBT will be assessed with the Implementation Leadership Scale [134]. ∙ Supervision competency will be measured by the Supervision Evaluation and Supervisor Competence Scale [135].	Director, provider, and supervisor surveys	baseline, 4 m, 8 m, 12 m, 24 m
Provider-level implementation targets	∙ Provider LGBTQ-affirmative CBT competency will be measured using the LGBTQ-affirmative CBT Knowledge Scale [57]. ∙ Provider motivation to implement LGBTQ-affirmative CBT will be measured with the adapted Measure of Innovation-Specific Implementation Intentions [136]. ∙ Providers’ LGBTQ counseling competency will be assessed with the skills subscale of the Sexual Orientation Provider Competency Scale [137]. ∙ Providers’ familiarity and experience with case conceptualization will be assessed by a seven-item questionnaire developed for this study.	Provider surveys	baseline, 4 m, 8 m, 12 m, 24 m
	∙ Clients’ perceived therapeutic alliance will be measured with the Working Alliance Inventory [114]. ∙ Clients’ perceptions of therapist efficacy in LGBTQ-affirmative CBT skills will be assessed with the adapted Sexual Orientation Counselor Competency Scale [113].	Client surveys	baseline, 4 m, 8 m, 12 m, 24
Effectiveness outcomes			
Client mental health	∙ Depression and suicidality will be assessed with the Patient Health Questionnaire– 9 [88]. ∙ Anxiety will be assessed with the Generalized Anxiety Disorder Scale– 7 [89]. ∙ Substance use problems will be assessed with the Alcohol Use Disorder Identification Test– Consumption [90] and Drug Use Disorder Identification Test– Consumption [91].	Client surveys	baseline. 4 m, 8 m, 12 m, 24 m
LGBTQ-affirmative CBT targets	∙ Internalized stigma and LGBTQ identity affirmation will be measured using the Internalized Homonegativity and Identity Affirmation subscales of the Lesbian, Gay, Bisexual Identity Scale [92]. ∙ Social isolation will be assesed wtih the UCLA Loneliness Scale [138]. ∙ Emotion dysregulation will be assessed using the Difficulties in Emotion Regulation Scale– Short Form [139, 140].	Client surveys	baseline. 4 m, 8 m, 12 m, 24 m

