We hypothesize that these three additive training implementation strategies will predict respective graduated increases in implementation success at 4-, 8-, 12-, and 24-months post-training (see Figs. 1 and [67]). That is, we predict that reach, effectiveness, adoption, implementation, and maintenance will be higher in the Local Supervision condition relative to the Direct Training condition and that the Direct Training condition’s implementation outcomes will be higher than the Materials Only condition. Drawing on theories of organizational [68, 69] and provider [70–73] change, we also hypothesize that organizational (e.g., shared norms of the importance of EBP) and provider (e.g., self-efficacy for EBP delivery) factors will mediate the stronger impact of the more intensive training strategies on implementation success and client mental health outcomes. To facilitate this latter aim, in a subset of 15 LGBTQ community centers (five centers per condition), we will compare the three training implementation strategies in terms of client mental health symptom change from before implementation to 4, 8, 12, and 24 months after.

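### Adoption is defined among providers who were trained, a post-randomization group that can differ by strategy and is empty at baseline; the denominator should be all enrolled providers

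*Protocol article*

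**What the plan says.** Under Implementation outcomes, the article lists adoption among the secondary outcomes ("Secondary implementation outcomes include mixed-methods assessments of the reach, adoption, familiarity, modification, and maintenance of LGBTQ-affirmative CBT skills across centers") and refers the reader to Table 1 for the definitions. Table 1 defines adoption as "Percentage of providers who self-report practicing LGBTQ-affirmative CBT out of total who were trained" and schedules it at baseline and at 4, 8, 12 and 24 months. Reach, the row above, starts at 4 months.

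Adoption carries a directional hypothesis. The Background states that "we predict that reach, effectiveness, adoption, implementation, and maintenance will be higher in the Local Supervision condition relative to the Direct Training condition", and that Direct Training will in turn exceed Materials Only.

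On sequence, the Randomization section says "the 90 LGBTQ community centers will be randomized in a 1:1:1 ratio". The Mental health providers section then says "Following randomization, mental health providers working at or affiliated with enrolled LGBTQ community centers will be invited to register for the training", and adds: "To be eligible to attend the training, mental health providers must provide consent and complete the baseline survey". Follow-up surveys go to every provider: "Regardless of their engagement with their respective training intervention".

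The training differs by arm. Under Materials only, "providers randomized to the Materials Only condition will only receive access to the platform and manual". Direct Training adds 12 weekly live webinars, and Local Supervision adds supervision to those. Engagement is monitored in all three arms.

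**The concern.** Enrollment and training are separate steps, and the article expects some enrolled providers not to engage. How many engage may depend on whether the offer is a self-paced course, scheduled webinars, or webinars with supervision. A denominator of trained providers then conditions a between-strategy comparison on a consequence of the strategy. A strategy that few providers take up should score worse on adoption. With this denominator, non-engagers drop out of the calculation and poor uptake is hidden.

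The baseline entry adds a second difficulty. The baseline survey precedes training, so nobody has yet been trained in the study and the ratio has no denominator.

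At stake is the reading of one RE-AIM outcome in a trial that aims to identify the minimum training needed in low-resource centers.

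**Working it through.** The documents state no adoption rate, uptake rate or power for adoption, so there is no figure to reproduce. The check is algebraic, with assumed rates to show the range.

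**Inputs from the article.** 90 centers, 1:1:1, about six enrolled providers per center (Sample size justification for the provider outcome): 90 × 6 = 540, and 540 / 3 = 180 per arm. Type I error rate of 0.05 for secondary outcomes; sidedness is not stated and two-sided is assumed.

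**Notation.** For each arm, a = adopters / enrolled and u = trained / enrolled. If adopters are among the trained, the Table 1 measure is

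adopters / trained = a / u.

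Write M for Materials Only and D for Direct Training, and suppose aD > aM. The Table 1 measure puts M ahead when aM/uM > aD/uD, that is, when

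uD / uM > aD / aM.

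Reversal therefore needs an uptake ratio larger than the true adoption ratio. Equal uptake keeps the order.

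**Assumed cases** (all rates are assumptions):

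| Enrolled basis, M vs D | aD/aM | Uptake, M vs D | uD/uM | Trained basis, M vs D | Result |
|---|---|---|---|---|---|
| 30% vs 40% | 1.33 | 90% vs 90% | 1.00 | 33.3% vs 44.4% | order kept |
| 30% vs 40% | 1.33 | 80% vs 90% | 1.125 | 37.5% vs 44.4% | order kept, gap shrinks |
| 30% vs 40% | 1.33 | 60% vs 80% | 1.33 | 50.0% vs 50.0% | difference erased |
| 30% vs 45% | 1.50 | 50% vs 80% | 1.60 | 60.0% vs 56.3% | reversed |
| 40% vs 50% | 1.25 | 60% vs 80% | 1.33 | 66.7% vs 62.5% | reversed |
| 40% vs 40% | 1.00 | 60% vs 80% | 1.33 | 66.7% vs 50.0% | false difference for M |
| 40% vs 40% | 1.00 | 90% vs 60% | 0.67 | 44.4% vs 66.7% | false difference for D |

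In counts, the fourth row is 54/180 vs 81/180 of enrolled providers, and 54/90 vs 81/144 of trained providers.

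**Chance of a false signal.** Suppose the arms were compared by a two-sided 0.05 test of two proportions, with true adoption of 40% of enrolled providers in both. With uptake of 60% vs 80%, trained numbers are 108 and 144, and the false difference (66.7% vs 50.0%) is significant with probability 0.76. The article's ICC bound of 0.1, borrowed from the fidelity outcome, gives design effects 1 + (3.6 − 1) × 0.1 = 1.26 and 1 + (4.8 − 1) × 0.1 = 1.38, and the probability is 0.64. With uptake of 80% vs 90% (50.0% vs 44.4%) the probabilities are 0.16 and 0.13.

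**The case against.** The best reply is that *trained* here loosely means *enrolled*. The Directors section explains being enrolled as a provider as taking part in the training, and elsewhere study and training are named together as one opportunity. No completion threshold or per-protocol set is defined. In Materials Only the strategy is access itself, so no attendance event separates trained from untrained. The baseline entry also makes sense only if the denominator is enrolled providers. This reading is plausible and may be what the authors intended. But no passage states it, and the Mental health providers section separates enrollment from engagement.

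Other parts of the reply also stand:

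- The analysis section for provider outcomes names self-efficacy, competency, familiarity and use as the secondary outcomes to be modelled at 8 months. Adoption is not in that list, so the false-signal probabilities refer to a test that the article does not specify. The Background still commits to a ranking of the strategies on adoption.
- Every provider receives the manual, so a provider who skips the training could still practice the therapy. If such providers count in the numerator, the measure is not a proper proportion.
- An all-enrolled denominator does not give a fully clean comparison. Providers register after center randomization, and nobody is masked, so the number and type who enroll may also depend on the strategy.

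A reader might infer that uptake will differ between arms, that the arm with poorer uptake will look better, or that the ranking will reverse. The documents do not support this. They give no uptake rates, scheduled webinars could draw either more or fewer providers than a self-paced course, and modest differences in uptake leave the order intact.

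**Conclusion.** The point holds in limited form. Taken literally, the Table 1 definition conditions a hypothesized between-strategy outcome on uptake after randomization and has no value at baseline. If uptake differs between arms, the comparison is biased. Reversal requires the uptake ratio to exceed the true adoption ratio, on the assumption that adopters are among the trained. Because the documents give neither uptake nor adoption rates, the direction and size of any bias are unknown, and the tabulated cases only illustrate what is possible. If the authors meant enrolled providers, the defect is one of wording, and the same change cures it.

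Adoption is a secondary outcome. The primary fidelity outcome and its sample size are unaffected.

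**What to change.** In Table 1, define adoption at each time point as the percentage self-reporting practice of LGBTQ-affirmative CBT among all enrolled providers in the center, regardless of training engagement. State that the baseline value is prior use among those providers. Report any figure among training completers as descriptive only, with *completer* defined for each arm.

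Because enrollment follows unmasked center randomization, also report enrolled providers by arm against the number that directors anticipated before randomization. That count is already collected for stratification.

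The cost is one changed definition and one added descriptive table. No new data are needed, since all enrolled providers are already contacted at every follow-up; survey non-response needs handling as for any other provider-reported outcome. Where some enrolled providers do not train, adoption percentages will be lower than on the literal definition. If *trained* always meant *enrolled*, they will not change.
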